### Sample size

Taking PA level as the primary outcome, with reference to a meta-analysis by Conn et al. [37], the overall mean weighted effect size of patient education on PA level among 17147 patients with chronically diseases is 0.45. The sample size of the proposed study is calculated via G*Power calculator [38]. For a two-tailed test, with the desired statistical power of 0.80 and significance level of 0.05, the estimated sample size is 158. Although the attrition rates of five related studies were less than 20% [11, 12, 14, 15, 17], for conservative reason, an attrition rate of 20% is assumed. Hence, a total of 190 participants (95 participants per group) will be recruited in the study.

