### Randomisation, blinding, and concealment

Following the completion of informed consent and baseline data collection, eligible participants will be allocated into either experimental or control group with 1:1 allocation ratio by a computerised random number generator (Fig 2). The random allocation sequences will be generated by a research assistant not engaging in recruitment. The sequences will be put in sequentially numbered, opaque, sealed envelopes [39, 40]. Research assistants will draw the envelopes in sequence to determine participants’ group allocation. To minimise performance bias, research assistants will not acknowledge participants their group assignment. To avoid contamination, the two groups will receive their corresponding treatments at different times in a private room. In addition, the two groups will undergo data collections at different times. Participants will be instructed not to share their education materials to others following the intervention. To avoid detection bias, the research assistant who performs data collection will be blinded to the group assignment. Since the principal investigator (a nurse) is responsible for conducting the lecture of the experimental group, she is unlikely to be blinded.

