### Intervention

#### (1) Experimental group

A systematic review by Peiris et al. includes 11 studies which examined the effect of lifestyle intervention programme integrated with education and unsupervised PA among adults with metabolic syndrome [41]. The intervention period of these studies ranged from 12 to 144 weeks and the duration of at least three months enhanced the outcomes significantly. Hence, the intervention period will last 12 weeks. Participants in the experimental group will receive a self-efficacy-based, integrated exercise and cardiovascular health education programme conducted by the primary research nurse for 12 weeks. The intervention comprising a health education talk, a booklet, a tailor-made exercise video, a lecture video, and a set of one-way text messages is designed based on the self-efficacy theory and is validated by an expert panel which contains two associate professors, one assistant professor, one physiotherapist, one cardiac nurse specialist, one cardiologist and one registered dietitian, with all of whom having considerable experience in conducting studies on lifestyle modification. Contents of the talk are derived from regional and international guidelines on PA recommendation and ASCVD prevention [34, 35, 42–46]. The components of ASCVD prevention are based on the seven predictors of cardiovascular health included in the Life’s Simple 7, a prescription for health formulated by the American Heart Association [42]. While PA will be emphasised in the talk, other elements of ASCVD prevention such as healthy diet, smoking cessation, as well as management on weight, BP, cholesterol, and blood glucose will also be introduced. In Week 1, a nurse will deliver a 60-minute face-to-face health education talk to a group of four to six participants. During the talk, the nurse will educate the participants about the risk factors of ASCVD. Apart from that, each participant will be invited to share his or her experience of performing PA and offer comments to other participants (vicarious experience). During the discussion, the nurse will offer positive feedbacks based on their sharing (verbal persuasion). If the participants raise some negative experience or feelings in relation to PA, suggestions on how they can do PA better will be provided to change their perceptions and feelings (emotional states). In the end, the nurse will demonstrate a set of exercises tailor-made for the elderly and ask the participants to do the return demonstration (mastery experience). These simple exercises are at moderate-intensity and involve an integration of balance training, aerobic and muscle-strengthening activities using a chair and a towel. To fulfil the PA recommendations suggested by the World Health Organisation (a minimum of either 150-minute aerobic PA with moderate intensity or 75-minute aerobic PA with vigorous intensity or a proportional combination of both every week) [7], participants will be encouraged to perform these exercises twice a day, 25 minutes each time in which 5-minute warm-up and 5-minute cool down exercises will be included. To enhance the standardisation of intervention delivery, a tailor-made exercise video, in which a nurse and two elders taking the lead in performing the aforementioned exercises, will be displayed during exercise demonstration (mastery experience and vicarious experience). The exercise video begins with a series of mobility and stretching exercises as warm-up, followed by a series of fitness exercises, including chair aerobics (e.g. hip marching, arm raises, arm swings, and chest expansions), balance exercises (e.g. single-leg stance, and single-leg swings), muscle-strengthening exercises (e.g. sit to stand, calf raises, and leg extension) and towel exercises. The video ends with cool-down exercises which comprise breathing and stretching exercises. To facilitate participants to revise the education materials and practice the exercises at home, each of them will receive a 17-inch portable video player which contains a pre-recorded lecture video (containing the same content as the health education talk) and an exercise video following the talk (mastery experience). On the other hand, a booklet which contains the key points of the health education talk will be provided for the participants as reference (mastery experience). A telephone number will also be provided for the participants in case they have any question or worry regarding the programme (emotional states). To improve exercise adherence, experimental group will be required to document their PA patterns in an exercise log daily.

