## Discussion

This study will provide clues regarding the effect of an integrated exercise and cardiovascular health education programme guided by self-efficacy theory on exercise self-efficacy, PA levels and ASCVD-related outcomes among community-dwelling older adults at risk of ASCVD. In fact, the healthcare burden associated with ASCVDs is enormous and long-term. Health education is always regarded as one of the most cost-effective ways for prevention of ASCVDs among older adults in the community. If our self-efficacy-based intervention is proven to be effective in promoting PA for older adults, this can inform healthcare professionals the more effective teaching strategy when compared to the traditional approach. This teaching strategy can subsequently be applied to other health education programmes for older adults, thus motivating them to adopt a healthy lifestyle, with an ultimate goal of preventing ASCVDs among this cohort in the long-run.

Despite the programme being evidence-based and theory-driven, three limitations may likely arise. First, as the programme is conducted in Cantonese and Chinese, study applicability may be limited as foreign participants are excluded. Second, as participants need to undergo multiple data collection procedures, a higher absence rate may exist in the post-tests. Hence, a reminder message will be sent to remind participants the evaluation arrangement. Third, although several precautions have been made to prevent contamination, there is a potential risk that participants may know other group’s allocated treatment as they may be from the same centre.

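### The article states no rule on co-resident participants, so two members of one household can be randomised to opposite arms although the exercise video is meant for home practice

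*Protocol article*

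**What the plan says.** **Recruitment and eligibility.** The Data collection section describes a convenience sample from elderly community centres, reached by posters, centre staff and centre activities, and screened with a structured eligibility checklist. The Participants section lists five inclusion and three exclusion criteria. None concerns a spouse, a co-resident or a household member who is already enrolled.

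**Allocation.** The Randomisation, blinding, and concealment section states that "eligible participants will be allocated into either experimental or control group with 1:1 allocation ratio by a computerised random number generator". Sealed envelopes are drawn in sequence, and no household unit is described.

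**Home use.** The section on the experimental group says that "each of them will receive a 17-inch portable video player which contains a pre-recorded lecture video" as well as an exercise video, so that participants can revise and exercise at home. Exercise is encouraged twice a day for 25 minutes each time. A booklet and a daily exercise log are added; that these two are also used at home is implied, not stated.

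**Safeguards.** The arms have separate session times, a private room and separate data collection times. In addition, "Participants will be instructed not to share their education materials to others following the intervention". Group assignment is withheld from participants.

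**Acknowledged limitation.** The Discussion concedes that "there is a potential risk that participants may know other group" treatments, and gives attendance at the same centre as the reason. The home is not mentioned.

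**The concern.** The criteria (age 60 or above plus one risk factor such as hypertension or overweight) can be met by both members of a couple, and a centre that reaches one may reach both. If individual allocation splits the pair, the control member lives with someone who exercises to a 17-inch screen and is encouraged to do so twice a day for 12 weeks. The programme itself relies on vicarious experience, which the Theoretical framework section describes as gaining confidence from watching similar people succeed. A co-resident control could be exposed to that mechanism without any material changing hands.

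Two things are at stake. First, a control who takes up the exercises reduces the difference in PASE-C, the primary outcome. Second, a split couple can compare what each was given and work out the allocation, and PASE-C is self-reported.

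**Working it through.** **Inputs from the Sample size section.** The effect size is taken from a meta-analysis: "the overall mean weighted effect size of patient education on PA level among 17147 patients with chronically diseases is 0.45". The calculation is: "For a two-tailed test, with the desired statistical power of 0.80 and significance level of 0.05, the estimated sample size is 158".

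**Step 1: reproduce the plan's figure.** A two-sample t-test (noncentral t) with d = 0.45, two-sided alpha 0.05 and power 0.80 needs 78.49 per arm. Rounded up, this is 79 per arm, or 2 × 79 = 158, an exact match. Power at 79 per arm is 0.803. The recruited total of 190 is 158 × 1.20 = 189.6, rounded up, and covers attrition only. (Whether that is the right inflation for 20% attrition is a separate question.) Neither step allows for contamination.

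**Step 2: share of controls exposed.** Let h be the share of participants who enrol with a housemate. The article does not give h; I assume 0% to 20%. Under 1:1 individual allocation, the housemate of a paired control is in the experimental arm with probability of about 1/2. The exposed share of controls is therefore about h/2, which is 0% to 10%.

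**Step 3: diluted effect.** Let k be the fraction of the effect that reaches an exposed control. The expected contrast is d = 0.45 × (1 − k × h/2). The standard deviation is held fixed.

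**Step 4: power at 79 per arm, two-sided alpha 0.05.**

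| h (assumed) | Controls exposed | k (assumed) | d | Power |
|---|---|---|---|---|
| 0% | 0% | – | 0.45 | 0.803 |
| 5% | 2.5% | 0.5 | 0.4444 | 0.793 |
| 5% | 2.5% | 1 | 0.4387 | 0.782 |
| 10% | 5% | 0.5 | 0.4387 | 0.782 |
| 10% | 5% | 1 | 0.4275 | 0.761 |
| 20% | 10% | 0.5 | 0.4275 | 0.761 |
| 20% | 10% | 1 | 0.405 | 0.716 |

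To restore 80% power, the evaluable total would have to be 174 at d = 0.4275 and 194 at d = 0.405, against 158.

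**Step 5: correlation within pairs.** Let ρ be the within-household correlation of the outcome (not given). A pair in the same arm adds to the variance of the group difference when ρ is positive, and a split pair subtracts the same amount. Individual allocation makes about half the pairs of each kind, so on average the two effects cancel. If every pair is kept in one arm, the variance of the difference is multiplied by about 1 + hρ, or 1 + 0.20ρ at h = 20%.

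**The case against.** **This is silence, not error.** The article condenses a fuller protocol, and the screening checklist is not shown. A reader might infer that nothing prevents co-enrolment. The documents do not support that: the checklist could already contain such a question. What can be said is that the article sets out the eligibility criteria and the allocation method, and neither includes a household rule. That is enough for a recommendation.

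**The safeguards.** A reader might infer that all the contamination measures stop at the centre door. They do not. The no-sharing instruction concerns sharing with others in general, after the intervention, so it covers the home. It is a real mitigation, but it leaves open both split allocation and a co-resident seeing the exercises.

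**The authors' own limitation.** Spouses who attend one centre are a subset of the same-centre participants whom the Discussion already names. This stands: contamination was noticed, and only the home route is new.

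**The size.** No frequency of co-resident participants appears in the article, and both members would have to volunteer and meet every criterion. Full transfer is a worst case, because a control spouse does not receive the experimental group talk, the return demonstration, the 36 text messages or the Week 7 progress report. Both points stand, which is why the range starts at zero and half transfer is shown.

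**Masking and independence.** Both arms receive a 17-inch player, so the device alone reveals nothing; its content would. A reader might also infer that paired participants make the planned standard errors too small. Step 5 shows no such direction under individual allocation.

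**Conclusion.** The point holds as a gap in the stated eligibility and allocation rules, not as a demonstrated flaw in the result. Controls can be exposed at home; how many will be is unknown. For an assumed 0% to 20% of participants enrolled with a housemate, power at the planned 79 per arm falls from 80% to about 72% at worst with full transfer of effect, or about 76% with half transfer. With few couples the loss is about one or two percentage points. The figures rest on the plan's d = 0.45, random splitting of pairs and an unchanged standard deviation.

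A reader might infer that the trial is underpowered because of this, or that a positive finding would be unsafe. Neither follows. The loss depends on a share that the article does not give, and dilution pulls the difference towards zero, so it cannot by itself produce a false positive. The possible effect of unmasking on self-report is not quantified here. This is a cheap improvement.

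**What to change.** Add one eligibility line, that no other member of the same household is enrolled in the trial, and one matching question to the existing structured checklist. This leaves the design contrast at 0.45 as far as the home route is concerned and needs no change to the analysis. The cost is that a few volunteers are turned away.

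If couples are needed to reach 190, obtain consent and baseline data from both members first, then open a single envelope for the household, and cluster on household in the GEE. Enrolling both beforehand matters because otherwise the second member's arm would be known at entry. The cost is the variance factor of about 1 + hρ from Step 5, slight if couples are few.

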#### (2) Control group

A placebo-controlled intervention will be provided to participants in the control group. Particularly, they will receive a 60-minute face-to-face health education talk on basic health issues. Information regarding PA and cardiovascular health education will not be provided during the talk. A 17-inch portable video player which contains a pre-recorded lecture video regarding the placebo health education talk and a corresponding governmental leaflet will be delivered as reference. Aside from receiving SMS reminder messages on attending the talk and data collection, no other SMS messages will be sent.

The primary research nurse will be responsible for preparing the education materials for both groups. Also, the health education talk of the experimental group will be conducted by the primary research nurse. For the control group, the talk will be conducted by another registered nurse. To ensure standardised lecture delivery, a training session will be provided to the nurse who engages in lecture delivery of the control group. Also, 10% of the intervention will be audio-recorded for quality control. To reduce subject contamination, the talk will be conducted in a private room and the two groups will receive their session at separate times.

### Data collection

For the consideration of data collection period, the systematic review by Peiris et al. indicated that the timing of outcome measurement among 11 included studies regarding lifestyle modification ranged from 12 to 144 weeks, with 24 weeks being mostly adopted in the effective studies [41]. Hence, in this study, the outcomes will be measured at baseline and Week 24, with extra measures at Week 12 and Week 36 added to serve as the interim and follow-up evaluations respectively. Convenience sampling will be employed for subject recruitment. A recruitment poster will be displayed in the elderly community centres. Older adults who are interested to join the study can contact the staff at the centres who will subsequently make referral to the research team. In case of having activities in which many older adults will be involved, the principal investigator will be present at the elderly centres to promote the programme. Potential participants will be approached by a research assistant face-to-face and participant eligibility will be screened via completing a structured eligibility checklist in the elderly community centres (-T_1_). After confirming the eligibility and providing the study’s details, written consent will be obtained and baseline data (T_0_) will be collected. After that, participants will be randomly assigned to either experimental or control group and will subsequently receive corresponding treatments. Participants will complete three follow-ups face-to-face at the elderly community centres at Week 12 (T_1_), Week 24 (T_2_), and Week 36 (T_3_). To ensure data reliability, research assistants who engage in data collection will receive a training session on the entire data collection procedure, procedures of physiological assessments and ways of assisting participants in completing questionnaires. Training PowerPoint slides will be provided to outcome assessors after the training session for reference.

### Outcomes

The effects of the integrated health education programme on PA level, exercise self-efficacy, and ASCVD-related outcomes will be examined. PA level throughout 24 weeks, which is measured with the Chinese version of the Physical Activity Scale for the Elderly, will be the primary outcome while others will be secondary outcomes.

#### (1) The Chinese version of the Physical Activity Scale for the Elderly (PASE-C)

The participants’ total PA level will be quantified with the PASE-C because of its comprehensiveness in measuring PA in various settings and its specificity for the elderly. This questionnaire will ask the participants to report the leisure, physical, household, and work-associated activities in the past seven days [51]. The PASE-C has been used in Asian populations aged 60 or above [52, 53] and possesses satisfactory test-retest reliability [54].

#### (2) The Chinese version of the International Physical Activity Questionnaire (short form) (IPAQ-C)

This questionnaire will document self-reported physical activity in the last seven days. Based on the collected data, participants can be classified into “inactive”, “minimally active” or “health enhancing physical activity active” via calculating the number of days and the total volume of PA by intensity. This questionnaire is widely used, cost-effective, possesses satisfactory reliability and comparable psychometric properties with the long form [55–57].

#### (3) The Chinese version of Self-Efficacy for Exercise (SEE-C)

This scale will be used to assess the participants’ self-efficacy to perform PA. The psychometrics of the SEE-C has been assessed in Chinese populations, with satisfactory internal consistency [58, 59].

#### (4) ASCVD-related outcomes

We will assess the following ASCVD-related outcomes: BP, fasting blood glucose, fasting blood lipids (low-density lipoprotein cholesterol, high-density lipoprotein cholesterol, and triglycerides), weight, BMI, waist circumference, and cardiac endurance. BP will be measured in a sitting position using calibrated, automatic BP monitor for two times. Participants will take a 5-minute rest prior to the measurement and 1-minute interval will be provided between each measurement [60]. Average of two measurements will be reported [11, 16]. Height will be recorded using a stadiometer while weight will be assessed using a calibrated scale, with results corrected to the nearest 1 cm and 0.1 kg respectively. Waist circumference will be measured two times in a standing position at the midpoint between the upper point of the iliac crest and the bottom of the last rib using a soft measuring tape [61]. Average of two measurements will be reported and corrected to the nearest 0.1 cm. Blood glucose and blood lipids will be measured via obtaining finger-prick blood samples using an auto-analyser. Participants are required to fast 8 hours before obtaining blood samples. A Two-Minute Walk Test will be used to assess the participants’ cardiac endurance. We will record the maximum distance that the participants can cover in two minutes [62]. This test is easy to implement and possesses satisfactory and comparable psychometric properties with a Six-Minute Walk Test, Timed Up and Go Test and Berg Balance Scale among older adults [63–65].

The evaluation results of BP, heart rate, Two-Minute Walk Test, BMI, weight, and waist circumference assessed at the screening stage will be included as the baseline data. As the systematic review by Peiris et al. [41] revealed that it took more than 3 months for lifestyle modification programmes integrated with unsupervised PA to cause significant impacts on fasting blood glucose, while another systematic review by Aucott et al. [66] indicated that lifestyle modification programmes targeted at weight loss might have positive impacts on long-term lipid profile, these two outcomes will be both measured at baseline (T_0_), Week 24 (T_2_), and Week 36 (T_3_) only.

